### Recruitment process

Participants will be employees of the authors’ University. They will be recruited through email, posters and flyers posted on the university campus. Basic information about the intended program will be provided and those interested will be invited to complete a short online survey assessing their burnout and vigor at work, usual PA and some demographic information. Based on existing cut-off scores on the Shirom Melamed Burnout Measure (SMBM) and the Shirom Melamed Vigor Measure (SMVM) (obtainable at http://www.shirom.org/arie/index.html), inclusion criteria for participation will be: a) being above the first tercile of the SMBM (i.e., scoring ≥1.79 on the SMBM Burnout total score), b) being below the third tercile of the SMVM (i.e., scoring ≤ 5.00 on the SMVM Vigor total score). Exclusion criteria will be a) employees currently receiving or having received in the last six months pharmacological treatment for mental health disorders, b) having contraindications to exercise, and/or c) engaging in regular demanding physical training for competitive sports (i.e., Level 4 using the Saltin-Grimby PA Level Scale; see [69]). Eligible participants will receive a randomly assigned participant number and the informed consent form that they will have to read and sign. They will also be invited to complete a second online survey assessing some of the baseline measures: job characteristics, recovery experiences during leisure activities, work ability, job satisfaction, work performance. Participants will be randomized to one of the four conditions (see below). Then twice a week for ten weeks participants in the three activity conditions will take part in activities on the university campus. In the first session, a baseline cardiorespiratory fitness test will be conducted for all the participants.

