### Randomization and blinding

Participants will be randomly assigned to one of the four conditions. A laboratory engineer will carry out the randomization once all participants are included, using the random function of Excel® software. Then, a second randomization will be done with the next 60 participants. A laboratory engineer will carry out the randomization, using the random function of Excel® software. In order to reduce bias, participants in PA conditions will not know their motivational style allocation (i.e. PA-TS or PA-NSS), and the instructor of each PA condition will not know the existence of the other condition. Finally, research assistants collecting data will be blinded to the treatment allocation.

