### Measures

Table 1 provides an overview of the measurement points of the primary and secondary outcomes, mediators, moderators and control variables, and manipulation check variables. At the end of the second session of each week, participants will complete a questionnaire measuring their weekly burnout, vigor, needs satisfaction at work and workload, as well as recovery mechanisms experienced, affects and effort perception during sessions (only for the 3 intervention groups). Five minutes are requested to complete the questionnaire. In week six of the program, participants will complete an online survey measuring job characteristics, and intervention groups will wear a 3-axis accelerometer to assess their energy expenditure during PA or theatre sessions. In week eight of the intervention, all instructors will be recorded audio-visually and participants will complete an online survey assessing their instructor’s motivational style during the sessions. At the beginning of the final session of the intervention participants will replicate the cardiorespiratory fitness test, and at the end of the intervention, participants will complete an online survey measuring the same variables as those assessed at baseline. Finally, three and six months after the end of the intervention, participants will be invited to complete the follow-up online questionnaire. In order to measure the *compliance* to the program, instructors from the three intervention groups will be asked to indicate the participants’ presence or absence at each session in a register.

**Table 1 Tab1:** Overview of the measurement points for the primary and secondary outcomes, during intervention and weekly measures, and follow-up measurements

	Variables	Pre-intervention (T0)	During intervention (T6 or T8)	Weekly (T1-T10)	Post-intervention (T11)	Follow-up at 3 and 6 months (T12–13)
Primary outcomes	− Burnout	✓		✓	✓	✓^a^
	− Vigor	✓		✓	✓	✓^a^
Secondary outcomes	− Job satisfaction	✓			✓	✓^a^
	− Work motivation	✓			✓	✓^a^
	− Work performance	✓			✓	✓^a^
	− Work ability	✓			✓	✓^a^
Psychological and physiological mediators	− Off-job recovery activities	✓			✓	
	− Psychological detachment	✓		✓^a^	✓	
	− Relaxation	✓		✓^a^	✓	
	− Control	✓		✓^a^	✓	
	− Mastery	✓		✓^a^	✓	
	− Relatedness	✓		✓^a^	✓	
	− Positive Affects			✓^a^		
	− Cardiorespiratory Fitness	✓			✓	
Moderator variable	− Compliance to activity sessions			✓^a^		
Control variables	− Job characteristics	✓	✓(T6)	✓^b^	✓	

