### Statistical analysis

#### Analyses of Primary and secondary outcomes

Between-arm differences in changes on the primary and secondary outcomes will be analyzed using generalized linear mixed models (GLMM) according to intention-to-treat and per-protocol principles. Intention-to-treat analyses [91] refer to the effect of treatment “as assigned”, meaning that all participants who are randomized to a condition will be included in the analyses, regardless of dropout or missing values. By contrast, per-protocol analyses refer to the effect of treatment “as received”, excluding only participants who have less than 50% compliance to the 20 sessions in the intervention. GLMM has several advantages over repeated measures ANOVA as it considers the hierarchical nature of the data and can accommodate missing data [92]. To distinguish between short- and long-term intervention effects, two separate series of GLMM analyses were performed for each outcome variable. Two time points (pre and post) were used to determine short-term intervention effects and four time points (pre, post, three- and four-month follow-ups) were used to examine long-term intervention effects. Regarding the short-term intervention effects, differences in changes on the outcome variables as a function of the group allocation will be assessed with models including group, time, and group x time interaction as fixed effects. For the group allocation, contrasts analyses [93] will also be carried out to test our hypotheses (H1 – H4) specifically. For that, three contrasts will be computed. The first one will compare the WLC condition with the Theatre condition, PA-TS and PA-NSS conditions (respectively coded as − 0.75, + 0.25, + 0.25, + 0.25) to test whether doing a leisure activity (PA or Theatre conditions) at the workplace leads to a reduction in burnout and an improvement in vigor (H1a, H1b). The second contrast will compare the Theatre condition with the PA-TS and PA-NSS conditions (respectively coded as − 0.667, + 0.333, + 0.333, while WLC will be coded 0) to test whether PA is more effective than theatre condition (H2) in reducing burnout and improving vigor. Finally, the third contrast will compare the PA-TS condition with the PA-NSS condition (respectively coded as − 0.50, + 0.50, while WLC and Theatre conditions will be coded 0) to test whether the positive effect of PA is more pronounced when the instructor uses a need-supportive style (H3). The same analyses will be performed to examine if the effects of the intervention are still effective three months (T12) and six months (T13) after the end of the intervention period. Since there are more than two-time measurements per participant, we will allow random intercepts for participants and random linear slopes for the repeated measurements at the level of participants. These random effects will allow us to estimate each participant’s outcome variables and the rate of change of these outcomes over time. In all analyses we will control for a number of variables that could influence participants’ outcomes. These include job characteristics, and needs satisfaction-frustration at work. Finally, an estimate of the effect size for each outcome will be reported using the conditional pseudo R^2^, which will be computed using the MuMin package of the R software [94].

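### Burnout and vigor at T0 appear to be the scores used for selection, so regression to the mean cannot be separated from a lasting effect at 3 and 6 months, when the waiting list is not measured

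*Protocol article*

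**What the plan says.** In the Protocol article, Recruitment process, "those interested will be invited to complete a short online survey assessing their burnout and vigor at work". Entry requires "being above the first tercile of the SMBM" (score at least 1.79) and "being below the third tercile of the SMVM" (score at most 5.00). Eligible people then receive a second survey, before randomisation, "assessing some of the baseline measures: job characteristics, recovery experiences during leisure activities, work ability, job satisfaction, work performance". Burnout and vigor are not in that list, yet Table 1 shows both at T0.

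At T11, according to Measures, "participants will complete an online survey measuring the same variables as those assessed at baseline", so the waiting list is included. At three and six months, Table 1 marks burnout and vigor with footnote a, which restricts them to the intervention groups. Analyses of Primary and secondary outcomes nevertheless repeats the same analyses "to examine if the effects of the intervention are still effective three months (T12) and six months (T13"). Those analyses include the contrast of the waiting list with the three activity arms. The Abstract and the Measures text describe follow-up without excluding the waiting list.

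**The concern.** People admitted because of a high burnout score and a low vigor score are admitted partly because of measurement error and passing fluctuation on that occasion. Their next score improves on average with no intervention at all. If the selection score is also T0, that improvement is part of every change from T0.

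While a randomised control is measured at the same times, this does no harm to the comparison: the drift is equal in expectation in all arms. At T12 and T13 that control is missing under Table 1. The long-term question is whether benefit persists relative to no activity, and the data for it would be change since T0 in the activity arms, which carries the drift with nothing to subtract it.

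**Working it through.** **Is the selection score T0?** Three texts bear on this. The screening survey measures both outcomes. The second survey names five kinds of variable and neither outcome. Table 1 requires both at T0. The screening score is therefore the only pre-intervention score described. The second list is introduced as covering only some baseline measures, and it also omits work motivation and needs satisfaction, which Table 1 has at T0. Re-use is the likely reading, not a stated fact.

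**What the plan's d = 0.35 and .5 refer to.** A repeated-measures group-by-time test with f = 0.35/2 = 0.175, alpha 0.025, power 80%, four groups, two time points and correlation .5 needs 111 participants, or 112 in equal groups; 112 × 1.25 = 140, the stated figure. So .5 is the pre–post correlation and d = 0.35 is a between-arm effect. The sample size is not affected by this point.

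**Size of the drift.** Assumptions: normal scores, cut-offs at the terciles of the reference population, stable true scores, independent errors, retest correlation r.

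- Burnout criterion alone: the mean of the upper two thirds is φ(−0.43)/(2/3) = 0.545 SD above the reference mean. Expected fall = (1 − r) × 0.545, which is 0.27 SD at r = .5 and 0.16 SD at r = .7.
- Both criteria, true burnout–vigor correlation −0.3 to −0.7 (simulation): 0.23–0.25 SD at r = .5, 0.18–0.20 at r = .6, 0.13–0.15 at r = .7. By symmetry vigor rises by the same amount.
- The SD in the selected sample is about 0.70 of the reference SD, so 0.24 reference SD (r = .5, true correlation −0.5) is 0.24/0.70 = 0.34 selected-sample SD. If the plan's .5 is the correlation within the selected sample (reference r about 0.64), the fall is about 0.24 selected-sample SD.
- With a T0 measured again after selection, the drift is 0.00.

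**Effect on tests.** Simulated false-positive rates with no true effect, 26 completers per arm and nominal 0.025, at r = .5 / r = .8:

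| Comparison | Rate |
|---|---|
| Group × time, T11 | 0.025 / 0.027 |
| Waiting list vs activity, T11 | 0.030 / 0.027 |
| Theatre vs PA, T13 | 0.022 / 0.024 |
| Change T0 to T13, activity arms pooled, no control | 0.49 / 0.16 |

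**The planned waiting-list contrast over four time points.** With time as a category, the waiting list has no data at T12 and T13 and the contrast there cannot be estimated. With a linear time effect it can be fitted, but it is biased. Code time 0, 1, 2, 3 and let the drift be a fall of δ by T11 and flat afterwards.

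- Waiting-list slope from two points: −δ.
- Activity slope from four points: −δ(−0.5 + 0.5 + 1.5)/5 = −0.3δ.
- Difference, activity minus waiting list: +0.7δ, or 0.7 × 0.24 = 0.17 SD per time unit.

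The waiting list would seem to improve faster. In a mixed model with random intercepts and slopes at r = .5, this contrast was rejected in about 11% of 120 simulated trials at nominal 2.5%, against 2.5% with a fresh T0. The Monte Carlo standard error is √(0.11 × 0.89/120) = 0.029. A repeat with 300 trials gave about 7% and 1%, and a mean bias of 0.17. The inflation is real, but its size is only roughly known.

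**The case against.** The strongest reply is that nothing in the plan tests within-arm change: the analysis is by randomised contrasts, and regression to the mean cancels in them. That stands for all contrasts at T11, and for Theatre versus PA and PA-TS versus PA-NSS at T12–T13. The waiting-list data at T0 and T11 even show how large the drift is. The reply fails only for waiting list versus activity at follow-up, where the control data are absent.

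It can also be said that the real defect is the missing waiting list, since season and natural course are left uncontrolled too. That is right, and a fresh T0 does not restore a control. It does remove the one component that the selection itself creates.

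Four stronger readings are tempting and are not supported:

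- That the article says the screening score is T0. It does not, and a condensed article may leave survey content to the full protocol.
- That selection on T0 costs precision at T11. The pre–post correlation does fall, from .50 to about .37, against about .42 with a fresh T0. But the variance of change falls as well. It is (1 − r)² × 0.70² + (1 − r²) = 0.87 at r = .5, against 2(1 − r) = 1.00 with a fresh T0; at r = .7, 0.55 against 0.60.
- That the drift can be set against d = 0.35 as a rival effect. The drift is shared by all arms, whereas d = 0.35 is a between-arm difference.
- That the planned linear contrast would show a false lasting benefit. Its bias runs against activity; the false benefit arises only if change since T0 is read as an effect.

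Randomisation is to be done "carry out the randomization once all participants are included", so some T0 scores may be old by the start of the programme. No duration is given, a second randomisation is also described, and randomisation balances any ageing.

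**Conclusion.** The point holds for the follow-up only. If the selection scores are T0, which is likely but not stated, every within-arm change contains regression to the mean. At T12–T13 the plan as written has no waiting-list data to remove it from the comparison with no activity. The spurious fall in burnout is about 0.13 to 0.25 reference SD for retest correlations of .5 to .7. These correlations and the normal model are assumptions, and the cut-offs are external: if burned-out employees volunteer preferentially, fewer are excluded and the drift is smaller. The primary T11 comparison and the contrasts between activity arms are sound. The change is worth making because the long-term conclusion depends on it and the cost is small.

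**What to change.** - State when T0 burnout and vigor are measured. If they come from the screening survey, add the SMBM (14 items) and SMVM (12 items) to the second pre-randomisation survey, use that score as T0 in all analyses, and keep the screening score for eligibility only. If a wave has already started, do this for the next 60 participants.
- Reconcile Table 1 footnote a with the analysis section. Either measure the waiting list at T12–T13, or drop its contrast there and limit follow-up conclusions to contrasts between activity arms. In the second case, do not present change from T0 to T12 or T13 as evidence of a lasting effect.

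Cost: 26 extra items in a survey already planned, with no new visit. An unadjusted change comparison would have about 5–15% more variance (1.00/0.87 = 1.15 at r = .5; 0.40/0.38 = 1.05 at r = .8). A baseline-adjusted analysis would instead gain about 4–6%.

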### Sample size

Sample size calculations were based on an a priori power analysis based on a previous study carried out on similar primary outcomes in the workplace [37, 66]. This study has reported a positive effect of the PA intervention on the emotional exhaustion component of burnout, with a small effect size (η^2^ = 0.03; f = 0.176). According to this result, we conducted an analysis with G*Power software [70] examining the evolution of burnout and vigor depending on the conditions as inter-individual factors, with an moderate effect size of d = 0.35, a statistical power of 80%, a threshold of significance at *p* < 0.025 considering our two primary outcomes, a correlation of .5 across repeated measures, and a potential dropout rate of 25% for a 10-week program with 4 groups. The results of this analysis recommend recruiting a minimum of 140 participants, 35 per group.

### Randomization and blinding

Participants will be randomly assigned to one of the four conditions. A laboratory engineer will carry out the randomization once all participants are included, using the random function of Excel® software. Then, a second randomization will be done with the next 60 participants. A laboratory engineer will carry out the randomization, using the random function of Excel® software. In order to reduce bias, participants in PA conditions will not know their motivational style allocation (i.e. PA-TS or PA-NSS), and the instructor of each PA condition will not know the existence of the other condition. Finally, research assistants collecting data will be blinded to the treatment allocation.

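### No equal-split or stratification rule is stated for allocation and no T0 adjustment is named in the analysis, so burnout and vigor scores known before randomisation go unused

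*Protocol article*

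**What the plan says.** Under Randomization and blinding, the protocol article says: "Participants will be randomly assigned to one of the four conditions". The method is "A laboratory engineer will carry out the randomization once all participants are included, using the random function of Excel". The section continues: "Then, a second randomization will be done with the next 60 participants", again with Excel's random function. It names no ratio, block, stratum or equal-split step, and does not state the size of the first batch.

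Under Sample size: "The results of this analysis recommend recruiting a minimum of 140 participants, 35 per group".

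Under Recruitment process, before allocation, "those interested will be invited to complete a short online survey assessing their burnout and vigor at work". These scores decide eligibility. The second online survey lists some of the remaining baseline measures and does not list burnout or vigor again, so the screening score may also be the T0 value. That is an inference.

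Under Statistical analysis, the short-term model has group, time and their interaction as fixed effects, with pre and post as the two outcome occasions. The covariates named are job characteristics and need satisfaction at work. The outcome's own T0 value is not among them, whereas the mediation models do control for baseline levels.

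**The concern.** Randomising a complete list in a batch is the easiest setting in which to secure both equal arms and balance on the primary outcomes: everyone is known and has a burnout and a vigor score before anyone is allocated. The stated procedure uses none of this, and the stated primary model does not recover it afterwards. At stake is precision in arms of 35, further reduced by an expected 25% dropout. A visible T0 gap between arms would also make the results harder to interpret.

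**Working it through.** **Inputs from the article:** 4 arms; minimum N = 140 (35 per arm); second batch 60; correlation .5; d = 0.35; significance level .025; dropout 25%. **Assumptions:** first batch 140 - 60 = 80; two occasions (pre, post); unit SD at each occasion; blocking score equal to the T0 score.

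**1. The plan's own figure.** 4 x 35 = 140. A repeated-measures within-between interaction with f = 0.35/2 = 0.175, two occasions, correlation .5, level .025 and power 80% needs 112 in equal groups, and 112 x 1.25 = 140. The target thus presumes four equal groups.

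**2. Arm sizes if each person is drawn independently (80 + 60, probability 1/4 each).**
- SD of one arm's size = sqrt(140 x 0.25 x 0.75) = 5.1.
- Simulation: exactly 35 in all four arms, 0.0006; some arm below 30, 0.52; median smallest arm 29, median largest 41.
- Cost: the variance of the PA-TS versus PA-NSS contrast rises 2% on average (19% or more in the worst 5% of draws). Overall relative efficiency (harmonic mean of arm sizes) is 0.98 at the median and 0.94 at the 5th percentile. At that percentile, power falls from 0.903 to 0.881 with 140 analysed, or from 0.775 to 0.744 with 105.

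**3. T0 balance if the list is shuffled and split into equal arms.** The SE of a T0 difference between two arms of 35 is sqrt(2/35) = 0.239 SD. The chance that a T0 gap exceeds 0.5 SD on each planned contrast is:
- PA-TS v PA-NSS: SE 0.239, 3.6%
- Theatre v both PA arms: SE sqrt(1/35 + 1/70) = 0.207, 1.6%
- WLC v the other three: SE sqrt(1/35 + 1/105) = 0.195, 1.0%

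For PA-TS v PA-NSS, a gap above 0.35 SD has probability 0.14.

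**4. Carry-over into the change contrast.** With equal SDs, the expected change difference given a T0 gap D is (correlation - 1) x D = -0.5 D. A gap of 0.35 SD therefore shifts the change contrast by 0.5 x 0.35 = 0.175 SD, half the planned d of 0.35.

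**5. Precision of the PA-NSS versus PA-TS contrast, 35 per arm.**
- Change analysis: SE = sqrt(2(1 - 0.5) x 2/35) = 0.239.
- Adjusted for T0: SE = sqrt((1 - 0.5^2) x 2/35) = 0.207; simulation gives 0.208. The reduction is 1 - 0.208/0.239 = 13%.
- In general the SE ratio is sqrt((1 + correlation)/2), so the gain is 19% at correlation .3, 13% at .5 and 8% at .7.

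**6. Which change produces the gain (simulation at correlation .5).**
- No blocking, change analysis: true SE 0.239, reported SE 0.239, type I error 2.4% at a nominal 2.5%.
- Sorted blocks of four, change analysis: true SE 0.208, reported SE still 0.239, type I error 0.9%. The test is conservative and the intervals do not shorten.
- No blocking, T0-adjusted: SE 0.208.
- Sorted blocks, T0-adjusted: about 0.207.

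The gain comes from the adjustment, not from the blocking.

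**The case against.** A reader might infer that allocation is unrestricted. The article does not say so. The same Excel function can shuffle a finished list for cutting into four equal parts, and 35 per group points that way, as does the Theatre group of 15, which is 60/4 (the Nordic walking group of twelve fits neither reading). A condensed article may also leave the split rule to the full protocol. This stands, and the 52% figure is therefore conditional on independent draws.

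A reader might also infer that chance T0 imbalance biases the trial. It does not. Either form of randomisation is valid, and step 6 shows that the reported standard error already covers the imbalance. Nor should the worst gap among all four arms be used for size: it exceeds 0.5 SD in 16% of draws, but the plan tests three specific contrasts, for which the chance is 1.0% to 3.6%.

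Finally, stratifying is optional and adds almost no precision once T0 is in the model. That stands too. What remains is that the article states its primary model with T0 as an outcome occasion and no T0 adjustment, so the known score is used neither at allocation nor in the stated analysis.

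**Conclusion.** The point holds as an inexpensive improvement, not as an error that threatens validity. As written, nothing secures 35 per group or balance on burnout and vigor. Unequal arms, if they occur, usually cost about 2% in variance. The larger loss lies in the analysis: a standard error of about 0.239 SD where 0.208 SD is available. Since the variance ratio is (1 + 0.5)/2 = 0.75, 35 per arm with adjustment is worth about 35/0.75 = 47 per arm without it.

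These sizes rest on the plan's correlation of .5, equal SDs and 35 analysed per arm. Dropout scales both standard errors alike and leaves the 13% unchanged. The balance gained by blocking would be smaller if T0 is measured separately from screening.

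**What to change.** - **Allocation.** State the rule for each wave. For any wave not yet randomised, sort the complete list on screening burnout, or on a burnout-vigor composite since both are primary. Cut it into consecutive blocks of four and permute the four conditions within each block, with a saved seed. This gives 20 + 15 = 35 per arm if the waves are 80 and 60; the 80 is inferred and should be stated.
- **Analysis, in all cases.** Analyse the post-intervention outcome adjusted for its T0 value, by ANCOVA or by a mixed model with T0 means constrained equal across arms. Adding the score only as a main effect to the group x time model would not change the contrast, because a term constant over time drops out of the change. Use the same treatment of T0 in the follow-up models.
- **Do both together.** Blocking without adjustment leaves the reported standard error too large.

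The cost is a short script and a revised model statement. No extra participants or measurements are needed.
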